### Outcomes: Secondary Outcome Measures

#### Somatic Symptom

The Somatic Symptom Scale-8 [52] can assess the somatic symptom burden during the previous 7 days. This scale includes 8 items rated on a 5-point Likert scale (0=not at all to 4=very much) with no reverse-coded items. The total score, ranging from 0 to 32, is the sum of all item scores, with a higher score indicating more severe somatic symptoms. The Japanese version of the Somatic Symptom Scale-8 has demonstrated acceptable reliability in a sample of Japanese individuals aged 20-64 years [53].

#### Cognitive Flexibility

The Cognitive Flexibility Scale (CFS) [54] is used to measure cognitive flexibility and considers an individual’s ability to produce diverse ideas, conceive response alternatives, and modify behaviors to adapt to changes in circumstances [55]. The CFS is a 12-item self-report questionnaire using a Likert-type scale ranging from 1=strongly disagree to 6=strongly agree. Each item in this questionnaire contains a sentence regarding beliefs and feelings about the respondent’s behavior. Total scores range from 12 to 72, with higher scores indicating greater cognitive flexibility. A previous study has confirmed the reliability and validity of the Japanese version of CFS among a sample of Japanese individuals [56].

#### Self-Esteem

Self-esteem will be measured using the Rosenberg Self-Esteem Scale [57], which consists of 10 items, such as “On the whole, I am satisfied with myself.” and “At times, I think I am not good at all.” Responses to these items are rated on a 4-point Likert scale (1=strongly disagree to 4=strongly agree). Mimura and Griffiths [58] have confirmed the reliability of the Japanese version.

#### Self-Compassion

The Self-Compassion Scale [16] is a 26-item assessment of the levels of self-compassion across 6 subscales (self-kindness, self-judgment, common humanity, isolation, mindfulness, and overidentification). Participants will be asked to rate the frequency of certain behaviors corresponding to each subscale. Responses range from 1=almost never to 5=almost always. The Self-Compassion Scale has good internal consistency, and its total score exhibits high convergent and discriminant validity [16]. The Japanese version of this inventory has high reliability and validity [59].

#### Perceived Stress

The Perceived Stress Scale-14 (PSS-14) is a self-report questionnaire intended to measure the degree of stress perceived by an individual in their life within the past month [60,61]. The PSS-14 consists of 14 items measuring how unpredictable, uncontrollable, and overloaded individuals feel about their circumstances. Participants rate each item on a 5-point Likert-type scale ranging from 0=never to 4=very often. Scores are obtained by reverse scoring the positively stated items and then summing the scores across all 14 items. The scores range from 0 to 56, with higher scores representing more significant perceived stress. Sumi [62] translated the Japanese version of the PSS-14 and confirmed its reliability and validity.

#### Well-Being

Life satisfaction will be assessed using the 5-item Satisfaction With Life Scale (SWLS) [63]. The SWLS items are rated on a 7-point Likert scale from 1=strongly disagree to 7=strongly agree, with higher scores indicating greater satisfaction with regard to one’s well-being. Its reliability and validity were substantiated by Pavot et al [64]. The Japanese version of the SWLS has been used in cross-cultural studies [65].

#### Emotion Regulation

The Cognitive Emotion Regulation Questionnaire is a 36-item scale measuring cognitive emotion regulation strategies to cope with the experience of threatening or stressful events or situations [66]. It evaluates 9 facets of cognitive handling strategies: positive reappraisal, putting into perspective, rumination or focus on thoughts, acceptance, self-blame, positive refocusing, other blame, catastrophizing, and refocus on planning. A 5-point Likert scale ranging from 1=almost never to 5=almost always is used to evaluate cognitive emotion regulation strategies. A validated Japanese version of the questionnaire will be used in this study [67].

#### Work Engagement

The Japanese version of the 9-item Utrecht Work Engagement Scale-9 can assess work engagement, which is defined as “a positive, fulfilling, work-related state of mind that is characterized by vigor, dedication, and absorption” [68-70]. Work engagement is assumed to be negatively correlated with burnout, and the 2 can be considered “opposites,” in that they represent a positive and a negative aspect of work-related well-being [70]. This scale includes measures of vigor, dedication, and absorption on a 7-point Likert scale from 0=never to 6=all the time. Each subscale comprises 3 items, and the scores of all are summed to determine the work engagement scores. The Utrecht Work Engagement Scale-9 has been translated into Japanese with adequate internal consistency and factorial validity [70].

#### Trait Anger

The State-Trait Anger Expression Inventory-2 is a 57-item questionnaire developed to measure the characteristic styles of coping with anger arousal using 5 components [71]. The 5 subscales include state anger, trait anger, anger-in, anger-out, and anger control. In this study, the participants will rate 10 items of the trait anger domain on a 4-point Likert scale ranging from 1=I strongly disagree to 4=I strongly agree to assess their degree of anger.

#### Psychological Safety

Psychological safety will be measured using the 7-item Psychological Safety Scale [72,73]. Psychological safety is defined as “being able to show and employ one’s self without fear of negative consequences to the self-image, status or career” [74]. Participants rate the items on a 7-point Likert-type scale ranging from 1=not at all to 7=strongly agree.

#### Creativity (Self-Perceived Creativity Scale)

The idea generation aspect of creativity in the workplace is assessed using 3 items from George and Zhou’s [75] scale modified for a self-report instrument by Dul et al [76]. This scale has been translated into Japanese and is used with the original authors’ permission. It includes the following 3 items for measuring employee creativity, which are scored on a 7-point Likert scale ranging from 1=do not agree to 7=agree: “In my work, I often have new and innovative ideas,” “In my work, I often come up with creative solutions to problems,” and “In my work, I often suggest new ways of performing work tasks.”

### Outcomes: Weekly Measures

#### Affect

The Affect Grid [77], which is used to assess emotional aspects, is a single-item scale designed as a quick means of assessing respondents’ affect along the dimensions of pleasure-displeasure and arousal-sleepiness. This scale evaluates the affect in a 2D structure consisting of 9×9 squares, with pleasure-displeasure on the horizontal axis and arousal-sleepiness on the vertical axis. The pleasure scores range from 1=unpleasurable to 9=highly pleasurable, and the arousal scores also range from 1=sleepy to 9=highly aroused.

#### Positive and Negative Emotions

The Positive and Negative Affect Schedule (PANAS) is used to measure the degree to which participants experienced positive and negative emotions within the past week [78]. The PANAS includes 20 items (10 positive and 10 negative emotions) that are rated on a 5-point Likert scale ranging from 1=not at all to 5=extremely. The Japanese version of this scale has demonstrated high reliability and validity [79].

### Outcomes: Daily Measures

Subjective psychological indices (relaxation) and physiological indices (HR and HRV) will be measured before and after daily meditation. The rating scale of relaxation will be used to assess the degree of participants’ relaxation [80]. This scale comprises 4 items, each of which is rated on a 10-point scale. Participants are required to “[select] the number from 1 to 10 that best describes [their] current state.” The 4 items are as follows: 1=feeling high to 10=stable, 1=tense to 10=relaxing, 1=anxiety to 10=relief, and 1=restrictive to 10=free. Nedate and Agari [80] used the average of the 4 scores as the relaxation score, which will be calculated similarly in this study as well (for more information on HR and HRV measurements, see the *Data Collection and Management* section).

### Participant Timeline

Participants who agree to participate in the study with informed consent and meet the inclusion criteria are assigned to the SCM, MM, or waitlist group. Participants are not notified as to which group they are assigned. All participants will then receive a web-based pretreatment assessment questionnaire at baseline via email and will be asked to complete it. Simultaneously, the participants assigned to the active arm (SCN and MM) will be asked via email to download and start using the smartphone app used for the intervention. Four weeks after the start of app use, participants will be sent a web-based posttreatment questionnaire by email and asked to complete it. Participants in the waitlist group will receive a web-based posttreatment questionnaire 4 weeks after they respond to the initial baseline questionnaire. Participants in the waitlist group will be asked to download and start using the smartphone app via email, distributed with the posttreatment questionnaire. All the participants in the waitlist group will be randomly assigned to the SCM and MM groups. During the 4-week intervention, all participants will be asked to respond to daily and weekly assessments of the smartphone app. Table 1 presents the schedule of procedures.

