### Assignment of Interventions: Allocation

Randomization will be performed after obtaining informed consent and screening the participants. It will be computerized and independently carried out by research staff using a blocked randomization scheme (block size 15) to ensure the seamless participation of those who apply to participate in the study. Eligible participants will be randomized into the SCM, MM, or waitlist group in a ratio of 1:1:1.

Participants are assigned to either the intervention (SCM or MM) or control (waitlist) condition immediately after randomization. The intervention will begin approximately 1 week after allocation. No specific instructions are given to the waitlist group, and they will be asked to wait for 4 weeks.

Interested candidates will be asked to confirm their consent to participate in this study and complete a screening questionnaire via web forms. The screening questionnaire consists of the K6 and items based on the inclusion criteria. Participants who meet the inclusion criteria are immediately included in the blocked randomization scheme and assigned by the research staff. After the participants have been assigned, they will receive an email with instructions to participate or wait.

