HR and HRV measurements will be taken on the smartphone app used for the intervention. Participants will be provided a sample and instructed to gently press their index finger against their smartphone’s camera for 30 seconds. At this time, the smartphone’s flash will turn on. By capturing the finger illuminated by the flash with the smartphone camera, HR and HRV will be measured. The procedure was set up based on a study that used HR and HRV measurements to evaluate the effectiveness of psychological interventions similar to this study [81]. HR and HRV will be measured using contact photoplethysmography, which is a noninvasive and convenient optical biomonitoring technique used to detect pulsatile changes in blood volume that appear in the microvascular bed of tissues [85]. The contact photoplethysmography method uses a white LED flashlight built into a smartphone and a rear camera to illuminate the skin for 30 seconds and detect light absorption due to arterial pulsation in the finger pad (Multimedia Appendix 3). For measuring HRV, the root mean square of successive differences—a measure of the square root of the mean squared difference between consecutive normal heartbeats—is used. The average HR measured in beats per minute is analyzed for HR.

When participants do not answer a questionnaire (baseline, preintervention assessment, and postintervention assessment), they will receive automatic reminders via email 6 days later. Participants who do not respond at baseline and preintervention assessment will receive further reminders after 13 days. If the participants are found not to respond to the questionnaire, they will be considered dropped by 14 days at baseline and preintervention assessment and by 7 days at postintervention assessment.

The data collected through the web-based forms are stored on a secure server with restricted access at the University of Tokyo. After data collection, this study will use a study-generated identification for data management, analysis, and publication. The list linking identifications to the participants’ personal information is stored on a hard disk disconnected from the internet, and the hard disk is kept in a locked cabinet.

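### The app request goes out with, not after, the questionnaire at both ends of the controlled period, so some active baseline and waitlist posttreatment scores may follow app use and dilute the active-versus-waitlist contrast

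*Protocol article*

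**What the plan says.** All references are to the protocol article.

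- **Order at the start.** Participant Timeline assigns participants first. It continues: "All participants will then receive a web-based pretreatment assessment questionnaire at baseline via email and will be asked to complete it". For the active arms the next step is "Simultaneously, the participants assigned to the active arm (SCN and MM) will be asked via email to download and start using the smartphone app".
- **Order at the end.** The same section says: "Participants in the waitlist group will be asked to download and start using the smartphone app via email, distributed with the posttreatment questionnaire".
- **What participants know.** Assignment of Interventions: Allocation says: "After the participants have been assigned, they will receive an email with instructions to participate or wait". The Blinding section accepts that people can work out their group from those instructions.
- **How late an answer may be.** Data Collection and Management sends non-responders a first reminder ("they will receive automatic reminders via email 6 days later"), and says that "they will be considered dropped by 14 days at baseline and preintervention assessment and by 7 days at postintervention assessment".
- **Text pointing the other way.** Allocation also says: "The intervention will begin approximately 1 week after allocation". Table 1 places the pretreatment assessment before week 1 and the posttreatment assessment before the waitlist's course. Interventions says the waitlist gets no intervention while it waits.
- **Clocks.** For the active arms, "Four weeks after the start of app use, participants will be sent a web-based posttreatment questionnaire by email". The waitlist's questionnaire is timed 4 weeks from its baseline response instead.

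**The concern.** The primary analysis compares pre-post change between groups by repeated measures ANOVA. That comparison needs an untreated pre score in every arm and an untreated post score in the waitlist. Table 1 and the Interventions section show that this order is intended, but the procedure in Participant Timeline does not secure it. The app request and the questionnaire travel together, and no sentence makes one wait for the other.

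If meditation helps, an active pre score given after some days of use already holds part of the benefit, and so does a waitlist post score given after its course has begun. Both reduce the estimated difference in change.

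Separately, active participants have been told to start before they give their baseline self-report. Their answers could shift for that reason alone, in a direction that cannot be predicted.

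**Working it through.** **1. Largest overlap allowed by the stated windows**

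| Score | Window | Overlap with app use |
|---|---|---|
| Active pre, app request sent with questionnaire (Participant Timeline) | 14 days | up to 14 of 28 days |
| Active pre, questionnaire at allocation and app use a week later (one reading of Allocation) | 14 days | 14 − 7 = about 7 days |
| Waitlist post, as a postintervention form | 7 days | up to 7 of 28 days |
| Waitlist post, only if treated as the waitlist's preintervention form | 14 days | up to 14 of 28 days |

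Because the active post form is timed from app start, an active baseline given t days into use also shortens that arm's pre-post interval to 28 − t days (14 days when t = 14). The waitlist keeps about 28.

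**2. The plan's own sample size**

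Sample Size gives f = 0.15, correlation 0.5, 3 groups, 2 occasions and 80% power; Statistical Methods gives alpha 0.05. With λ = f²·N·m/(1 − ρ), df1 = 2 and df2 = N − 3:

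λ = 0.0225 × 111 × 2 / 0.5 = 9.99, and power = 0.803 at N = 111.

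This reproduces the stated 37 per arm.

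**3. Loss of effect from late answers (illustration)**

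Assumptions, none of them in the protocol: app use starts when the request arrives; benefit grows linearly to B at day 28; the active post score is given at day 28; the waitlist gains at the same rate. K6 asks about the past 30 days, so a K6 answered on day t of use carries the average benefit over that window:

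C(t) = (1/30) ∫₀ᵗ B·s/28 ds = B·t² / (2·28·30)

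Share of the day-28 effect lost = C(t)/C(28) = (t/28)².

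- t = 7: (7/28)² = 6.25%
- t = 14: (14/28)² = 25%

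The 28-day recall of the WHO-HPQ replaces 30 by 28, which cancels, so the shares are the same. If only a share p answers late, the loss is p·(t/28)²; half answering at day 7 gives 0.5 × 6.25% = 3.1%. A waitlist post score at day 7 costs a further 6.25%. With everyone late at both ends, the total is 12.5% (days 7 and 7) or 31.25% (days 14 and 7). The protocol does not state the recall period of the Stanford scale, so no figure is given for it.

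**4. What that does to power at N = 111**

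If the interaction is wholly active versus waitlist (assumption), f falls in proportion to the loss.

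| Loss of f | Power |
|---|---|
| 0 | 0.803 |
| 6.25% | 0.747 |
| 12.5% | 0.684 |
| 25% | 0.542 |
| 30% | 0.483 |

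The share of late responders, which determines the row that applies, is not in the protocol.

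**The case against.** Four objections carry weight.

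- **The intended order is stated.** Table 1 and the Interventions section give it, and the one-week lag may separate questionnaire and app start. This stands as far as it goes: it supports about 7 days rather than 14 as the active maximum on one reading. It does not remove the overlap. The lag runs from allocation rather than from the questionnaire, it is shorter than the 14-day window, and Participant Timeline calls the two e-mails simultaneous.
- **Recall blunts the effect.** This stands. A reader might infer that up to half the effect is lost, since 14 of 28 days is 50%. That needs a score reflecting only the state on the day, and everyone answering at the cut-off after two reminders. With the stated K6 and WHO-HPQ recall periods the same extreme gives 25%.
- **The bias is conservative.** Under a true benefit, the treatment overlap pulls towards no difference and cannot create one. Weeks 1 and 2 are the same in SCM and MM, so that comparison is little affected. The exception is a reporting shift from knowing one's group, whose direction is open.
- **Enrolment reached 375.** More participants recover power, but they do not remove dilution from the estimate.

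A reader might also infer that losing baseline non-responders breaks the randomised set. Non-response at baseline does fall after randomisation, but Other Analyses says all participants are included and missing values replaced where applicable, whereas the Primary Outcome paragraph requires both assessments. That is a separate question about the analysis set and is not shown by the timing alone.

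**Conclusion.** The point holds as a weakness of sequencing. As written, the procedure permits active baseline scores after up to 14 days of app use (about 7 on the more favourable reading) and waitlist posttreatment scores after up to 7 days. The documents do not establish 14 days for the waitlist; that depends on which window its month-1 form falls under, which is left unclear.

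Under a true benefit, the active-versus-waitlist contrast is diluted. On linear accrual averaged over recall, a late active baseline costs about 6% if all answer at day 7 and 25% if all answer at day 14, and proportionately less if only some are late. The actual loss is unknown. Since the expected direction is towards the null, the frequency is not known and one comparison is largely spared, this is should-fix: it limits how a small or null result can be read rather than invalidating the trial.

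**What to change.** **Text.** Reconcile Interventions, Table 1, Participant Timeline, Allocation, and Data Collection and Management. Preferably the full baseline battery is completed before allocation, in the web form that already holds the screening K6. At the least, the app link is released only when the questionnaire is submitted: baseline in the active arms, month 1 in the waitlist. State which response window applies to the waitlist's month-1 form. The cost is a longer form before allocation and some loss of applicants before randomisation instead of after it.

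**Data already collected.** The abstract reports data collection complete in late October 2023, so re-ordering helps only future use. For these data:

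1. Use the screening K6, which precedes randomisation, as the K6 baseline covariate. This costs only a change of model. It does not help the work-performance outcomes or the waitlist post score.
2. If questionnaire and first-use timestamps exist (the protocol does not say), report by arm how many baseline scores and waitlist post scores followed first app use.
3. Add a sensitivity analysis that sets those scores to missing within a model retaining all randomised participants, not a completer analysis. State that it conditions on behaviour after randomisation that differs by arm, so it supports the main analysis and does not replace it.

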### Data Collection and Management

The participants will be assessed for outcome measures via web forms at baseline (pretreatment assessment) and 1 month and 2 months after the course starts (posttreatment assessment and follow-up assessment, respectively). Additionally, the participants will complete weekly and daily assessments during their courses. As mentioned earlier, the weekly measures consist of 1 question from the Affect Grid [77] and 20 questions from the PANAS [78,79]. The daily assessment involves the degree of participants’ relaxation [80] and objective physiological measures (HR and HRV) on the smartphone app. Participants will be asked to perform daily assessments using the smartphone app before and after daily meditation. The weekly assessment will be measured via web-based forms once a week immediately after the 7-day meditations, and participants will receive an email requesting them to respond to the questionnaire and a reminder to use the self-care app. The web-based survey to be conducted in this study is designed with reference to the CHERRIES (Checklist for Reporting Results of Internet E-Surveys) checklist to ensure a complete description of web-based surveys (Multimedia Appendix 2) [84]. When reporting the results, we will provide a detailed report of what is described in CHERRIES.

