### Statistical Methods

#### Primary Outcome

The intention-to-treat approach involving participants who have completed pretreatment and posttreatment assessments will be used to test the effectiveness of the active arms compared to the waitlist group. To examine preintervention and postintervention changes and pre-post differences between the groups, the results of the assessment questionnaires will be analyzed using repeated measures ANOVA. The statistical significance level is set at *P*<.05 for all statistics. Analyses will be performed using SPSS (IBM Corp) and R (R Foundation for Statistical Computing).

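### The month-1 questionnaire runs from start of app use in the active arms but from the baseline response in the waitlist, so the pre-post interval, and on the natural reading who is sent the form, depends on arm

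*Protocol article*

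**What the plan says.** The Participant Timeline section sets two clocks for the same assessment. In the active arms: "Four weeks after the start of app use, participants will be sent a web-based posttreatment questionnaire by email". In the control arm: "Participants in the waitlist group will receive a web-based posttreatment questionnaire 4 weeks after they respond to the initial baseline questionnaire". The active arms receive the baseline form and the app invitation together: "Simultaneously, the participants assigned to the active arm (SCN and MM) will be asked via email to download and start using the smartphone app". Data Collection and Management again counts the posttreatment and follow-up assessments from the start of the course.

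Two other passages bear on timing. Assignment of Interventions: Allocation says "The intervention will begin approximately 1 week after allocation". Data Collection and Management says of non-responders that "they will be considered dropped by 14 days at baseline and preintervention assessment and by 7 days at postintervention assessment".

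Under Statistical Methods, Primary Outcome, "The intention-to-treat approach involving participants who have completed pretreatment and posttreatment assessments will be used". Other Analyses says instead that all participants are analysed. It counts people with minimal app use as completers, provided that they answer each questionnaire.

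**The concern.** The posttreatment assessment should fall at the same time after a common origin in every arm, and should be sought from everyone randomised. Here the origin in the active arms is something the participant does after randomisation, namely taking up the treatment. In the waitlist it is answering a questionnaire.

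Two things are at stake. First, time since baseline is not the same in the groups being compared. Second, if the clock starts only when a person opens the app, missing posttreatment data depend on uptake in the active arms and not in the waitlist. The primary comparison would then set active starters against all waitlist participants who answered, under an intention-to-treat label. The rule for minimal users in Other Analyses does not repair this: minimal use supplies a start date, but no use does not.

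**Working it through.** **1. The plan's own figure.** The Sample Size section requires 37 per arm for 80% power, with f = 0.15, correlation 0.5, three groups, two times and alpha 0.05. With noncentrality f² × N × 2/(1 − 0.5) and 2 and N − 3 degrees of freedom, the smallest N is 111 (37 per arm), with power 0.8035. At 40% attrition, 111/0.6 = 185, so 200 suffices (200 × 0.6 = 120 completers, power 0.836). The calculation reproduces and is not at fault.

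**2. Interval by arm.** Let L be the day of app start minus the day of the baseline response.

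- Waitlist, baseline response to dispatch: 28 days.
- Active arms: 28 + L days.

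The document does not give L. The app invitation goes out with the baseline form, that form stays open for 14 days, and no rule is stated that baseline must come first. L can therefore be as low as 0 − 14 = −14. No latest date for starting the app is stated, so there is no upper limit. For illustration:

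| Assumed L (days) | Active interval | Waitlist interval |
|---|---|---|
| −14 | 14 | 28 |
| −7 | 21 | 28 |
| 0 | 28 | 28 |
| +7 | 35 | 28 |
| +14 | 42 | 28 |

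The arms agree only at L = 0. With a negative L, baseline is recorded after treatment began. The K6 looks back 30 days and the WHO-HPQ 28 days, so the interval also changes how far the posttreatment recall window overlaps the pretreatment period.

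**3. Who has a send date.**

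| Participant | Month-1 send date under the written rule |
|---|---|
| Waitlist, baseline answered | Yes |
| Active, baseline answered, app opened once | Yes |
| Active, baseline answered, app never opened | None stated |

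The third row cannot enter a set defined by completed pretreatment and posttreatment forms.

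**4. Possible size.** The share s who never start is not in the document, so every figure here rests on an assumed s.

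- *Ratio of effects.* Suppose that never-starters gain nothing, and that starters and never-starters would change equally without treatment. If starters gain E, the all-randomised effect is (1 − s)E, and the starters-only estimate exceeds it by a factor 1/(1 − s). At s = 10% this is 1/0.9 = 1.11; at 30% it is 1/0.7 = 1.43.
- *Why that is a ceiling.* If all starters reply, and a fraction r of never-starters would reply when sent the form, the factor due to the sending rule is 1 + r × s/(1 − s). It equals 1/(1 − s) at r = 1 and falls to 1 at r = 0.
- *Shift in the mean.* If never-starters' mean change differs from starters' by 0.3 SD (assumed), omitting them moves the active mean by 0.3 × s: 0.015 SD at s = 5% and 0.09 SD at 30%.
- *Numbers.* Of 67 per active arm, s of 5%, 10%, 20% and 30% means about 3, 7, 13 and 20 people without a send date. If this comes on top of 40% attrition, completers are 67 × (1 − s) × 0.6 = 38, 36, 32 and 28, against 66 × 0.6 = 40 in the waitlist. If never-starters are already within the 40%, the total does not change. The article also reports 375 enrolled; if these were split equally, even s = 30% leaves 125 × 0.7 × 0.6 = 52.5 per arm. The issue is selection rather than power.

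**5. Reminder rules.** Of early non-responders, the plan says: "Participants who do not respond at baseline and preintervention assessment will receive further reminders after 13 days". Baseline and preintervention forms close at 14 days and postintervention forms at 7. The waitlist's month-1 form comes just before its own course, so it could fall under either label. The text does not settle which.

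**The case against.** The strongest reply is that no sentence says never-starters go without a posttreatment form. With the course beginning about a week after allocation and e-mails sent automatically, the start may be a scheduled date, and everyone would then be sent the form. A journal article may also leave a fallback send date to the full protocol. This stands as far as it goes: that never-starters are never sent the form is an inference from the written rule. But the rule names a participant's behaviour, contrasts it with another participant behaviour in the next sentence, and gives no calendar date. The scheduled reading would still leave the arms on different anchors.

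Three other stronger readings are tempting, and the document does not support them:

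- *The active interval is always longer.* It is not, because L can be negative.
- *The 11-43% is an estimate of bias.* It is a ceiling on an assumed share. Some people who never open the app would not answer a questionnaire either, and baseline non-responders are dropped in every arm, so some of the least engaged leave all groups by that route.
- *The waitlist's month-1 form is chased harder and longer.* This requires the preintervention assessment to mean that form. The Sample Size section uses the same term for the ordinary pre measure. It is an ambiguity, not a shown difference between arms.

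It is also fair that timing from app start lines the recall windows up with four weeks of use. That is a reason for the choice in the active arms, but it does not justify a different clock in the control arm. Finally, the effect on the primary result runs through the pre-post completer set, which conflicts with the all-participants statement in Other Analyses. That conflict is a defect in its own right. Resolving it towards all participants would keep never-starters in the analysis, but with outcomes missing according to uptake in the active arms only.

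**Conclusion.** The point holds in a limited form. The different anchors are explicit, and an arm-dependent pre-post interval follows from them on either reading of the start. The exclusion of active never-starters from the primary set follows on the participant-level reading, which is the natural one but is not stated outright. Neither the direction nor the size of any bias can be derived from the document. With an assumed 10-30% never starting, no gain in them and equal untreated change, 11-43% is the most that the sending rule could add to the effect. The point should be corrected because it touches the primary between-arm comparison.

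**What to change.** Send the month-1 questionnaire to every randomised participant 4 weeks after one anchor common to all arms, for example the scheduled course start or a fixed time from allocation, whether or not the app was opened. State one reminder schedule and one closing date for that time point in all arms, and say what the preintervention assessment means in Data Collection and Management. Bring Participant Timeline, Allocation, Data Collection and Management, and the two statements of the analysis set into line.

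The Abstract reports that data collection was completed in late October 2023, so the sending rule can no longer be changed for this trial. What remains possible is to report the baseline-to-post interval and the number of never-starters by arm, and to keep never-starters in the all-randomised analysis with missing outcomes handled by a stated method.

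The cost in a trial still running is a change to the e-mail schedule; here it is some tabulation and a missing-data method. N does not change. The downside of a common anchor is that slow starters are assessed before four weeks of use, and the 28- to 30-day recall windows then cover some untreated days, which slightly dilutes the effect.
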